|------|-------------------------------------------------------------------------------------------------------------------------------|
| 1711 | Do you smoke?  Yes  Smoked before but quit now  Never |
| 1712 | If yes:                                                                                                                       |
| 1713 | How many cigarettes did you smoke every day?                                                                                  |
| 1714 | How many years have you been smoked?                                                                                          |
| 1715 | Does your family members smoke?  yes  no                                      |

1716

1717 **ALCOHOL**

|      |                                                       |
|------|-------------------------------------------------------|
| 1718 | Alcohol consumption, during the past 3 months. |
| 1719 | How often do you drink? _____                         |
| 1720 | What kind of liquor do you often drink? _____         |
| 1721 | How much alcohol do you drink in one sitting? _____   |

1722

1723 **EXERCISE**

1724 **1** During the last 7 days, on how many days did you perform **VIGOROUS** physical activities, e.g., carry

1725 water, jog, run, farm, climb or fast bicycling? Think about only those physical activities that you did for at

1726 least 10 minutes at a time.

1727 \_\_\_\_\_ days a week ☐ (Go to 2)      No vigorous physical activities ☐ (Go to 3)

1728 **2** How much time did you usually spend doing **vigorous** physical activities on one of those days?

\_\_\_\_\_ hours per day

\_\_\_\_\_ minutes per day      Don't know/Not sure ☐

1729 **3** During the last 7 days, on how many days did you do **moderate** physical activities like carrying light  
 1730 loads, bicycling at a regular pace, or doubles tennis?  
 1731 \_\_\_\_\_ days a week ☐ (Go to 4) No moderate physical activities ☐ (Go to 5)  
 1732 **4** How much time did you usually spend doing **moderate** physical activities on one of those days? \_\_\_\_\_ hours  
 1733 per day  
 1734 \_\_\_\_\_ minutes per day Don't know/Not sure ☐  
 1735 **5** During the last 7 days, on how many days did you walk at least 10 minutes at a time? This includes  
 1736 walking at work and at home, walking to travel from one place to another, doing housework and any  

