## 3.3 Outcomes evaluation and measurement

The outcomes for follow-up assessment will be in the same way of the baseline and 12-month follow-up assessment. Table B-1 illustrate all the key aspects of measurement by comparing with baseline and 12-month follow-up assessment.

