2687 ☐ Not at all ☐ Not very much ☐ Fairly ☐ More ☐ Very much

2688 B8. Do you feel that you need to be cared for by other people or in other ways?

2689 ☐ Very much ☐ More than necessary ☐ Fair ☐ Less than necessary ☐ Not at all

2690 B9. For you and your partner, the amount of money you earn on your own in a year is:  
2691 \_\_\_\_\_

2692 ☐ Don't know

2693 B10. For you and your partner, the amount of social welfare income (retirement, pension,  
2694 benefits, etc.) for one year is: \_\_\_\_\_

2695 ☐ Don't know

2696 B11. For you and your partner, the amount of money given by your children in a year is:  
2697 \_\_\_\_\_

2698 ☐ Don't know

2699

2700 Please write the patient item number again ☐ ☐ ☐ ☐ ☐ ☐

2701

2702 **C: SMOKING**

2703 C1. Do you smoke (100 or more cigarettes in total)?

2704 ☐ Smoke (skip to C2) ☐ Used to smoke, but don't anymore (skip to C3)

2705 ☐ Never smoked (skip to C4)

2706 C2. How many cigarettes do you smoke on average in a day? (Please fill in the number)

2707 \_\_\_\_\_

2708 C3. When you used to smoke, how many cigarettes did you smoke on average in a day?

2709 (Please fill in the number) \_\_\_\_\_

2710 C4. In the past, how many years have you smoked in total? \_\_\_\_\_

2711 C4a. In which year did you stop smoking? If you stopped smoking in 2015, please enter "2015":

2712 \_\_\_\_\_

2713 C4b. Please enter the month in which you stopped smoking: \_\_\_\_\_

2714 C4. Is there anyone in the household who smokes regularly?

2715 ☐ Yes ☐ No

2716

2717 **D: EXERCISE**

2718 D1. How many days in the past 7 days has the patient engaged in vigorous physical activity (e.g.  
2719 carrying water, jogging, fast running, farming, fast cycling, etc.)?

2720 Please consider only those physical activities that lasted at least 10 minutes at a time. \_\_\_\_\_  
2721 days

2722 D2. On the days when there was vigorous physical activity as described above, how long was  
2723 the patient usually able to do vigorous physical activity each day? \_\_\_\_\_ minutes

2724 D3. How many days in the past 7 days has the patient engaged in moderate intensity physical  
2725 activity (e.g. brisk walking, lifting light objects, cycling, jogging, etc.)?

2726 Please consider only those physical activities that lasted at least 10 minutes at a time.  
2727 \_\_\_\_\_ days

2728 D4. On the days when moderate intensity physical activity as described above, how long was  

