2729 the patient usually able to do moderate intensity physical activity each day? \_\_\_\_\_ minutes

2730 D5. How many days in the past 7 days has the patient walk for at least 10 minutes at a time on  
2731 that day? (Includes walking at work, at home, from somewhere to somewhere, for recreation, for  
2732 leisure) \_\_\_\_\_ days

2733 D6. On the days when walking was available as described above, how long did the patient  
2734 usually spend walking each day? \_\_\_\_\_ minutes

2735 D7. How many hours did the patient sleep at night (not including time spent lying awake and not  
2736 including daytime naps)? \_\_\_\_\_ hours

2737 D8. How many hours in the past 7 days has the patient spend sitting or lying down  
2738 approximately (not including sleeping at night)? \_\_\_\_\_ minutes

2739

2740 **E: DIET**

2741 E1. How often do you eat vegetables on average?

2742 ☐ Every day (or >5 times a week) ☐ 2-5 times a week ☐ Once a week

2743 ☐ Less than once a week ☐ Never or hardly ever

2744 E2. How often do you eat fruit on average?

2745 ☐ Every day (or >5 times a week) ☐ 2-5 times a week ☐ Once a week

2746 ☐ Less than once a week ☐ Never or hardly ever

2747

2748 **F: FIRST BLOOD PRESSURE MEASUREMENT**

2749 Measurement should do the following:

2750 Step 1 Land on both feet

2751 Step 2. Right arm measurement

2752 Step 3. The upper arm and sphygmomanometer should be at the same level as the heart

2753 Step 4. The center of the balloon is located right in the brachial artery

2754 Step 5. Standard sleeves

2755 Fa Please enter the value of the first blood pressure measurement for systolic pressure (high  
2756 pressure): \_\_\_\_\_mmHg

2757 Fb Please enter the value of the first blood pressure measurement for diastolic pressure (low  
2758 pressure): \_\_\_\_\_mmHg

2759

2760 **H: HISTORY OF STROKE**

2761 Only consider strokes diagnosed by county hospitals and above

2762 H1. How many times have you been hospitalized for stroke in the last four months?

2763 H2. Has there been a recurrence of stroke in the past year? (based on hospitalization, any level  
2764 of hospitalization, only infusion without overnight stay in hospital does not count)

2765 ☐ Recurrence (skip to H2) ☐ No recurrence

2766 H3. Number of recurrences of stroke: \_\_\_\_\_. For each recurrence, complete the following  
 2767 information.

|                                     | 1 | 2 | 3 | 4 | 5 |
|-------------------------------------|---|---|---|---|---|

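### Appendix B2 words the vigorous and moderate activity durations as ability where Appendix A-3 asks time spent, which may weaken comparability of the long-term activity score

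*Combined protocol and SAP*

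**What the plan says.** Part A section 5.7 defines physical activity by what participants did in the past week, using the IPAQ short form. Table 4 turns this into MET-minutes per week and a binary HEPA class. Appendix A-3, titled as the questionnaire for baseline and follow-up, asks in item 2: "How much time did you usually spend doing vigorous physical activities on one of those days". Item 4 is the same for moderate activity. A don't-know box is printed beside the duration items.

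Part B section 3.3 states: "The outcomes for follow-up assessment will be in the same way of the baseline and 12-month follow-up assessment". Section 3.2.1 likewise asks assessors to measure consistently with the two earlier rounds. Section 3.3.2 lists physical activity as a secondary outcome, and section 3.4.1 adjusts the long-term analysis for the baseline outcome.

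In Appendix B2, D2 begins "On the days when there was vigorous physical activity as described above, how long was" and continues "the patient usually able to do vigorous physical activity each day". D4, tied to active days in the same way, asks how long was "the patient usually able to do moderate intensity physical activity each day". The walking item D6 keeps the behavioural form: how long did the patient "usually spend walking each day". None of D2, D4 and D6 prints a don't-know option.

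**The concern.** Time spent on an activity and time one is able to spend on it are different quantities. The second can exceed the first. Minutes multiply directly into the activity score, so a change of meaning in the duration item carries straight through. Within B2 the two phrasings sit in one score, because vigorous and moderate durations are worded as ability and walking as time spent. Part B already measures function separately through Timed Up and Go, ADL/IADL and the modified Rankin Scale, so an activity item that drifts toward ability would overlap with those.

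At stake is one Part B secondary outcome on a behaviour the intervention targeted. If the 5.5-year score does not measure the same thing as the baseline and 12-month scores, the trajectory across the three rounds is hard to interpret.

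**Working it through.** The plan gives no figure on this point, so there is none to reproduce. The check is a comparison of the two forms, followed by the effect on the score.

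**Step 1: items side by side**

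| Element | Appendix A-3, Exercise | Appendix B2, section D |
|---|---|---|
| Vigorous, days | Item 1: days performed | D1: days engaged in |
| Vigorous, minutes | Item 2: time spent doing | D2: how long able to do, on active days |
| Moderate, days | Item 3: days done | D3: days engaged in |
| Moderate, minutes | Item 4: time spent doing | D4: how long able to do, on active days |
| Walking, days | Item 5: days walked | D5: days walked |
| Walking, minutes | Item 6: time spent | D6: time spent |
| Don't-know option on minutes | Printed at items 2, 4 and 6 | Not printed at D2, D4 or D6 |

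The change of meaning is confined to two cells, the minutes for vigorous and moderate activity. The missing don't-know option is not a convention of the whole form, because B2 prints such an option at B9 to B11.

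**Step 2: how it enters the score**

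Leaving the MET weights aside, each component is proportional to days x minutes. Let r be the factor by which minutes on active days are overstated. The documents give no value for r. The values below are assumptions, and r = 1 means no effect.

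| Active days, 30 true minutes each | r = 1 | r = 1.25 | r = 1.5 | r = 2 |
|---|---|---|---|---|
| 0 | 0 | 0 | 0 | 0 |
| 1 | 30 | 37.5 | 45 | 60 |
| 3 | 90 | 112.5 | 135 | 180 |
| 7 | 210 | 262.5 | 315 | 420 |

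A person with no active days scores zero on that component whatever their capacity.

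**Step 3: change from baseline**

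Take someone at 3 days x 30 minutes in both rounds, so with no true change. The apparent change is 90r - 90: 0 at r = 1, 22.5 at 1.25, 45 at 1.5 and 90 minutes a week at r = 2. With the HEPA cut-off unchanged, inflated minutes can also move people across it.

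**Step 4: the contrast between arms**

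If the same r applies in both arms, the difference in a component's mean becomes r x (mean in intervention - mean in control). A true difference of zero stays zero, and a non-zero difference is rescaled. The baseline covariate still uses time-spent wording. If the wording lowers its correlation with the outcome, the adjustment removes less variance and precision falls.

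**The case against.** The strongest reply is that D2 and D4 are anchored to days on which the activity took place. On such a day, how long someone was able to keep going can naturally be read as how long they managed, which is what they did. That stands as a limit on the point. A reader might infer that the long-term score records capacity in place of behaviour; the documents do not support this. The day counts and all of walking remain behavioural, and only the minutes multiplier of two components is exposed.

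Second, the printed English may be a translation. Other lines in B2, such as the blood pressure instructions, read that way, and A-3 warns that its paper layout is imperfect. The field-language items are not in the documents, so what respondents heard cannot be settled. This also stands. It is a reason to check the wording, and it does not reconcile the two forms as printed.

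Third, some further inferences are tempting but unsupported:

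- **Bias toward the intervention arm.** Exercise encouragement might be thought to raise reported ability there. Both arms get the same items from blinded assessors, about four years after the active phase ended, and nothing in the documents shows a differential response.
- **Forced entry of a number.** Part A section 5.6 describes forced response. Part B names the same platform but does not state that setting.
- **The zero-day skip.** A-3 has one for vigorous and moderate activity and B2 does not, but with zero days the product is zero either way.
- **A percentage for the inflation.** If 30% of active participants answered for capacity at 1.5 to 2 times their true minutes, and resembled the others in true minutes, the component mean would rise by 0.30 x 0.5 = 15% to 0.30 x 1.0 = 30%. Neither the share nor the ratio has any basis in the documents.

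Finally, Part B section 3.2.1 requires consistent measurement and section 4.1 plans a pilot of the updated questionnaire. These give an opportunity to catch the discrepancy, but the form as printed still carries it.

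**Conclusion.** The point holds as a minor inconsistency in an instrument. D2 and D4 depart from the A-3 wording, and the don't-know option is gone, contrary to Part B's own statement of identical measurement. The possible result is inflated minutes in the vigorous and moderate components, with weaker comparability across rounds, distorted change from baseline and HEPA class, and a lower baseline correlation. This assumes that the field-language items match the printed English and that some respondents read them as asking about ability. If either assumption fails, the wording effect is zero, and nothing in the documents narrows the range above zero. Randomization and a common form protect the arm comparison from a spurious difference under a common factor, though not from rescaling or loss of precision. The primary outcomes are unaffected.

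**What to change.** Reword D2 and D4 to follow A-3 items 2 and 4, beginning "How much time did you usually spend doing" and ending with a reference to one of the active days. Restore the don't-know option there, and at D6 for consistency with A-3 item 6. Alternatively, document that the field-language items were identical at baseline, 12 months and the post-trial round. The pilot in Part B section 4.1 is a natural place to do either. The cost is two reworded items and a response option, or one documented check.

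If data were in fact collected with capacity wording, state in the report that comparability of the long-term activity score with baseline and 12 months is limited. That statement should depend on the check of the field wording; the printed English alone does not justify it.

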#### STROKE-RELATED INFORMATION

When were you first diagnosed with stroke (only those diagnosed by county-level hospitals and or above)?

Year: \_\_\_\_\_ Month: \_\_\_\_\_ Type: \_\_\_\_\_ Diagnosed by/at: \_\_\_\_\_

Have you had recurrent stroke since then (only including episodes requiring a visit to or hospitalization at county-level hospitals or above)? How many times?

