### 3.3.2 Secondary outcomes

The secondary outcomes of interests will be in line with the original protocol, including diastolic blood pressure, medication adherence (measured by using 4-item Morisky Green Levine Scale), physical activity level (measured by using IPAQ-short form), mobility (measured by using Timed-up and go test), health-related quality of life (measured by using EQ-5D-5L), disability (measured by using modified Rankin Scale), stroke recurrence (measured by self-reported experience of stroke recurrence) and stroke-related hospitalization (measured by self-reported history of hospitalization).

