| H4. Year                            |   |   |   |   |   |
| H5. Month                           |   |   |   |   |   |
| H6. Type of stroke                  |   |   |   |   |   |
| H7. Health facility attended        |   |   |   |   |   |
| H8. Whether hospitalized for stroke |   |   |   |   |   |
| H9. Days of hospitalization         |   |   |   |   |   |
| H10. Insurance reimbursement        |   |   |   |   |   |
| G11. Out-of-pocket expenses         |   |   |   |   |   |
| G12. Total expenses                 |   |   |   |   |   |

2768

2769 **I: HOSPITALIZATION FOR OTHER ILLNESSES**

- 2770 I1. In the past year, have you been hospitalized for any reason other than a stroke? (only  
2771 infusion without overnight stay in hospital does not count)
- 2772 ☐ Yes ☐ No
- 2773 I2. In the past year, how many times have you been hospitalized for reasons other than stroke?  
2774 \_\_\_\_\_
- 2775 I3. In the past year, what was the total number of days spent in hospital for reasons other than  
2776 stroke? \_\_\_\_\_
- 2777 I4. In the past year, what were the reasons for hospitalization other than stroke? (If multiple  
2778 hospitalizations, select all reasons for hospitalization)
- 2779 ☐ Heart disease (acute heart attack, angina, heart failure, coronary artery disease, etc.)
- 2780 ☐ Lung disease (acute pulmonary embolism, asthma, etc.)
- 2781 ☐ Blood system disease ☐ Kidney disease ☐ Tumour or cancer ☐ Trauma
- 2782 ☐ Other, please specify: \_\_\_\_\_
- 2783 I5. Has the following been newly diagnosed in the past year at a county or higher hospital? (ask  
2784 as fully as possible and tick all appropriate boxes)
- 2785 ☐ Hypertension ☐ Dyslipidemia ☐ Diabetes
- 2786 ☐ Serious heart disease (acute heart attack, angina, heart failure, coronary heart disease, etc.)
- 2787 ☐ Serious lung disease (e.g. acute pulmonary embolism, asthma, etc.)
- 2788 ☐ Tumor or cancer ☐ Hematological disorders ☐ Kidney disease
- 2789 ☐ Other diseases diagnosed at county level or above
- 2790 ☐ No diseases (other than stroke) diagnosed at county level or above

2791

2792 **J VILLAGE CLINIC (ASK ONLY ABOUT STROKE AS A MEDICAL CONDITION)**

- 2793 J1. In the past 12 months, how often did you visit the village clinic because of stroke on average  
2794 (including asking about your condition, taking blood pressure, getting medicine, controlling blood  
2795 sugar; not including preventive fluids, seeing other illnesses such as cold, upset stomach,  
2796 kidney disease, etc.)?

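### Part B's questionnaire counts a stroke recurrence only if the patient was admitted, although Part B says outcomes are measured as before and Part A also accepts a visit without admission

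*Combined protocol and SAP*

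**What the plan says.** Part B section 3.3 sets the general rule: "The outcomes for follow-up assessment will be in the same way of the baseline and 12-month" follow-up assessment. Section 3.3.2 lists two separate secondary outcomes: "stroke recurrence (measured by self-reported experience of stroke recurrence) and stroke-related hospitalization". The second is measured by self-reported history of hospitalisation. Neither recurrence nor its measurement carries an admission condition there. Table 4 of the SAP (Part A, section 7.3) likewise defines 12-month recurrence as a self-reported stroke event and lists stroke-related hospitalisation separately.

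The Part A questionnaire (Appendix A-3, headed for use at baseline and follow-up) qualifies recurrent stroke as "only including episodes requiring a visit to or hospitalization at county-level hospitals or above".

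The Part B questionnaire (Appendix B2, section H) opens with "Only consider strokes diagnosed by county hospitals and above". Item H1 then asks "How many times have you been hospitalized for stroke in the last four months". Item H2 asks "Has there been a recurrence of stroke in the past year? (based on hospitalization, any level", and its bracket continues "of hospitalization, only infusion without overnight stay in hospital does not count". For each recurrence reported, the form then records the facility attended (H7) and "H8. Whether hospitalized for stroke".

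**The concern.** Sections 3.3 and 3.3.2 promise a self-reported recurrence measured as before, but the item that collects it makes admission part of the definition. Nothing in sections 3.3 or 3.4 announces or justifies the change.

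Three things are at stake. Recurrences managed without admission drop out of the long-term outcome. A long-term recurrence result set beside the 12-month questionnaire result would compare two event definitions. And two secondary outcomes that appear to be separate evidence overlap by construction, because a recurrence counted under H2 is already a stroke admission.

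**Working it through.** The documents give no figure to reproduce on this point. The check sets the definitions against a few possible records and then shows, under stated assumptions, how the admission rule acts on counts and on the risk ratio.

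**Step 1: the definitions applied to records**

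| Record | Part A form (A-3) | Table 4 and Part B 3.3.2 | B2 section H header | B2 item H2 |
|---|---|---|---|---|
| New stroke, admitted overnight at a county hospital | counts | counts | passes | counts |
| New stroke, diagnosed at a county hospital, no overnight stay | counts | counts | passes | does not count |
| New stroke, admitted at a township hospital, also diagnosed at a county hospital | counts | counts | passes | counts |
| New stroke, admitted at a township hospital, no county-level diagnosis | does not count | counts (no level stated) | fails | counts on H2's own wording |

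The second row is the substantive conflict: the header lets the event through and H2 then removes it. Such cases are not merely theoretical. H2 excludes infusion without an overnight stay by name, and Part A's form names a visit as an alternative to admission. The fourth row is a conflict within section H: the header restricts the level of diagnosis, while H2 accepts any level of admission.

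**Step 2: how recurrence relates to stroke hospitalisation in Part B**

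- Every recurrence accepted under H2 is an admission, so H8 should be yes for each of them and adds nothing.
- H8 is filled in only for recurrences. An admission for stroke that was not a new event cannot appear there.
- H1 is asked independently of H2, but it covers four months and H2 covers one year.
- Section I covers past-year admissions for causes other than stroke. Part A's form, by contrast, listed every admission of the past 12 months with its diagnosis.

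Over one common year, recurrence under H2 is therefore a subset of stroke admissions. If hospitalisation is derived from H8, it adds nothing to H2. If it is derived from H1, it is a different quantity over a shorter window. Section 3.3.2 does not say which item is used.

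**Step 3: effect on counts (assumed shares)**

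Recorded recurrences = true recurrences × share admitted. The share is not in the documents, so a range is assumed:

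- 0.9: 100 × 0.9 = 90 recorded of every 100
- 0.8: 80
- 0.7: 70
- 0.5: 50

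**Step 4: effect on the risk ratio (assumed shares)**

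Recorded RR = true RR × (share admitted, intervention ÷ share admitted, control):

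- 0.8 ÷ 0.8 = 1.000: no change
- 0.9 ÷ 0.8 = 1.125
- 0.9 ÷ 0.7 = 1.286
- 0.7 ÷ 0.8 = 0.875

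The distortion arises only if the shares differ between arms, and it can go either way.

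**The case against.** A fair defence has several parts.

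- *An overnight admission is a reasonable specificity rule for self-report*, particularly as Part B section 3.2.3 allows proxy answers. The form applies the same infusion exclusion to non-stroke admissions in item I1. This stands as a reason to choose such a rule, but the rule then has to be stated in section 3.3.2, which says something else.
- *The 12-month comparator is itself uncertain.* Appendix A-3 asks about recurrence since the first diagnosis, whereas Table 4 confines the outcome to the 12-month follow-up. The appendix warns that the paper version is less consistent and clear than the electronic one, and it prints an 8-item adherence scale where the outcome is a 4-item scale. Part A section 5.6 and Table 3 also draw recurrence from insurance records, which section 5.6 describes as hospitalisation data. So Part A recurrence was partly admission-based, and the loss of comparability is firm only for the questionnaire-based outcome.
- *The hospital-level contrast is narrow.* A reader might infer that Part B dropped the county-level restriction. The section H header keeps it for diagnosis, so H2's reference to any level can apply only to where the patient was admitted. What remains is a wording conflict to reconcile.
- *The two outcomes are not the same variable.* A reader might infer full duplication. H1 asks separately about stroke admissions, and an admission without a new event belongs only to hospitalisation. Nesting is what the documents support.
- *Bias between arms is not shown.* A reader might infer it because intervention visits included referral. Supported visits ended in July 2018 (Part B section 3.1), H2 asks about a single year roughly four years later, and both arms answer the same form. Village doctors could continue the services voluntarily, so a difference cannot be excluded, but nothing in the documents establishes one or its direction.

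**Conclusion.** The conflict between item H2 and Part B sections 3.3 and 3.3.2, Table 4 and Part A's form is established from the wording alone. As written, H2 under-captures non-admitted recurrences, gives an outcome that is not like-for-like with the 12-month questionnaire outcome, and nests recurrence within stroke hospitalisation, so the two should not be read as independent evidence.

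The size of the under-capture cannot be obtained from the documents; the 90 to 50 per 100 above rests wholly on assumed admission shares. It would be tempting to attach event counts by combining the 11.2% first-year recurrence figure in the Background with 625 patients per arm. That is not supported: the percentage is a first-year rate, 625 is the planned baseline size (half of 1,250), and H2 is answered only by survivors assessed years later. With equal admission shares the risk ratio is unaffected and only events, hence precision, are lost.

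The point concerns secondary outcomes of the long-term follow-up and does not touch its primary outcomes, systolic blood pressure and mortality. It is still worth correcting, because it changes what the recurrence result means and the correction is cheap.

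**What to change.** If the form can still be changed:

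- Reword H2 to Part A's event definition: a stroke diagnosed at county level or above, whether through a visit or an admission. Remove the admission and overnight-stay conditions. This also reconciles H2 with the section H header.
- Give H1 the same one-year window as H2 and take stroke-related hospitalisation from it, as a question on all stroke admissions. Do not derive it from H8 alone: H8 is recorded only for recurrences, so hospitalisation would become a subset of recurrence.
- Add a sentence to section 3.3.2 naming the item and window behind each of the two outcomes.

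If the form has already been used: name the H2 outcome *hospitalised recurrent stroke* in section 3.3.2, state that it is nested within stroke hospitalisation, and do not compare it directly with the 12-month recurrence result.

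The cost is the wording of two items and one sentence in section 3.3.2; the fallback changes text only. The small downside of the rewording is that non-admitted events rest on self-report, as they already do in Part A.
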